## Abstract

**Background:**

Each year in the UK approximately 367,000 people are diagnosed with cancer of whom half will experience moderate to severe chronic pain and a third are undertreated for their pain. Most people with cancer are cared for at oncology outpatient services where there are no standardised approaches for managing pain. As a result, cancer patients are at risk of receiving inadequate care for pain. There is a need for a standardised approach to pain management within oncology outpatient services.

**Methods/design:**

The aim of this pilot trial is to establish the feasibility of conducting a multi-centre clustered-randomised trial of an integrated standardised pain assessment and management programme integrated within routine care at oncology outpatient services in the United Kingdom National Health Service (NHS).

We will conduct a two-arm pilot cluster randomised trial with nested process evaluation to evaluate the feasibility and acceptability of trial processes, establish fidelity of intervention implementation, estimate variability in outcomes and feasibility of future economic evaluation. Twelve outpatient services (clusters) from at least two NHS tertiary oncology referral centres (sites), in the North of England will be randomised (1:1) to deliver a pain management programme plus usual care or usual care alone and will recruit a total sample of 180 participants. Adults attending a participating outpatient service who self-report a score of ≥ 3 on the 0–10 Numerical Rating Scale (NRS) for worst pain in the past 72 h in any part of their body, and will be available for 1-week follow-up will be eligible. Participant self-reported questionnaires will be collected at baseline, 1-week, 1-month, and 2-months with medical record review at 1-month and 2-months. Progression to a future trial will be based on pre-defined criteria associated with eligibility and consent rates, follow-up and intervention delivery and acceptability.

**Discussion:**

Little research has described optimal ways to implement a standardised pain assessment and management programme into oncology outpatient services. The strengths of the pilot trial are its sample size, number of clusters, and planned evaluation of trial processes and intervention fidelity to provide robust trial evidence to fully inform a future definitive phase III multi-centre cluster randomised trial within the UK NHS.

**Trial registration:**

The CAPTURE pilot trial is registered on the ISRCTN registry (86,926,298).

## Background

Each year in the UK approximately 367,000 people are diagnosed with cancer. The prevalence of cancer-related chronic pain is estimated to be more than 70% [1]. Approximately 50% of all patients with cancer will experience moderate to severe cancer-related chronic pain (i.e. pain related to cancer and its treatment); and a third of patients with cancer are undertreated for their cancer-pain [2, 3]. Under-treatment of cancer pain reduces patients’ quality of life, [3] and increases healthcare service use and costs [4]. For patients, the burden of chronic cancer-related pain is associated with anxiety and depression, [5] significant reduction in physical and emotional wellbeing, as well as overall reduction in quality of life [6]. Clinicians report that a lack of awareness of pain management guidelines and poor knowledge about pharmacological pain management are the most common barriers to optimal pain management [7, 8]. At a service level, uncontrolled pain is the most common reason for cancer patients contacting GP out of hours services [9].

Numerous guidelines on managing cancer pain have been published in the last 25 years [1, 10]. Trial data indicate that adherence to these guidelines can improve quality of care and pain outcomes for patients with cancer. [11–15] However, in the UK the majority of people with cancer are cared for at oncology outpatient services where there are no standardised approaches for managing pain [10]. As a result, cancer patients receive inadequate and inconsistent care for pain [3, 16, 17]. Systematic review data highlight the need for a standardised approach to the assessment and management of chronic cancer-related pain [11, 18]. As the majority of cancer patients are cared for at oncology outpatient services, there is a clear need for a standardised approach to pain management within these services. This has been highlighted as an NHS health service priority [19, 20].

The Edinburgh Pain Assessment and management Tool (EPAT) was developed for use in a hospital ward setting [12]. EPAT is a simple cancer pain assessment and management tool designed to prompt clinicians to systematically assess and manage cancer pain across the duration of a care episode. Pain scores are used to guide clinical decision making and treatment using linked treatment algorithms. Therefore, EPAT is both a pain assessment and a pain management intervention. In previous implementation, EPAT significantly reduced cancer-related pain in patients on oncology wards and led to more appropriate analgesic prescribing, without higher doses [12].

EPAT consists of four core components: screening, detailed assessment, prescribing, and reassessment. EPAT was designed to be integrated into standard clinical practice by implementing it within existing policies on hospital oncology wards. As such, EPAT works optimally with the contextual factors associated with a hospital ward environment. Prior to the pilot trial, a theoretically informed process of contextual adaptation using the ADAPT guidelines [21] was undertaken to adapt EPAT from its original ward setting for use in oncology outpatient services. This involved a series of qualitative interviews to map existing pain management processes in oncology outpatient services [22]. In a co-design process involving oncology healthcare professionals, each component of EPAT was mapped onto the new setting to identify potential mismatch and subsequent need for modification. This was a key step in the process of adaptation [23]. Each stage of the research was informed by evidence and theory of complex intervention adaption [23–25].

Challenges to implementing optimal pain management procedures into oncology outpatient services remain. Mackhlouf et al. [8] demonstrated that oncology clinicians’ lack of pain management knowledge and fears of opioid addiction prevent effective cancer pain management. Adam et al. [11] demonstrated that basic pain intensity screening (using 0–10 scales) has little impact on pain outcomes for cancer patients or prescribing behaviour of clinicians. This was due, in part, to a lack of guidance for clinicians on how to use pain data. Oldenmenger et al. [13] and Williams et al. [14] both found that tailored pain education for patients attending oncology outpatient services did not lead to improved cancer pain management. A common feature of these two studies is the lack of an explicit implementation strategy to support integration and uptake of routine pain assessment (aimed at clinicians) and self-management information (aimed at patients). Implementing effective pain management processes within routine oncology outpatient services has yet to be successfully achieved and this will be the focus of the CAPTURE pilot trial.

### Overall aim

In the long term, we aim to establish whether a standardised pain management programme integrated within routine care at oncology outpatient services can reduce the impact of chronic pain on individual patients with cancer and the burden on out of hour’s services. To achieve this, we need to establish the feasibility of undertaking a definitive phase III multi-centre cluster randomised trial within the UK National Health Service (NHS).

### Objectives

The objectives of the CAPTURE pilot trial are to:Establish eligibility, recruitment, retention, and follow-up rates to inform the design of a future phase III RCT.Assess the acceptability of the intervention and protocol to healthcare professionals and patients with cancer.Assess the extent to which oncology healthcare professionals can deliver the intervention with competency and fidelity (i.e. deliver the components of the intervention as intended) following brief training.Gather preliminary data on the effect of the intervention via exploration of between-group change in outcomes.Establish the feasibility of an economic evaluation of EPAT and obtain preliminary estimates of cost-effectiveness.

## Methods

### Trial design

We will use a multi-centre, two-arm, pilot cluster randomised controlled trial, with a nested qualitative process evaluation. Twelve outpatient services (clusters) from at least two NHS tertiary oncology referral centres (sites) in the North of England will be randomly allocated (1:1) to deliver EPAT + usual care or usual care alone. 180 eligible patients will be recruited.

### Setting, clusters, and randomisation

Oncology outpatient services will be eligible for inclusion if they:Care for patients with a diagnosis of cancer.Do not currently have a standardised pain assessment and management programme integrated within routine practice.Provide written informed consent to support participation.

Each site will be required to have obtained local trust approvals and have undertaken a site initiation meeting within the trial team before services are randomised and participant recruitment starts. Following confirmation of eligibility, services will be randomised (1:1) to deliver EPAT plus usual care or usual care alone (Fig. 1) by the trial statisticians (MC, SG) at the Leeds Clinical Trials Research Unit (CTRU). Minimisation, incorporating a random element will be undertaken by hand to ensure treatment arms are balanced with respect to site, cancer type (i.e., breast vs. lung vs. prostate vs. bowel vs. upper GI vs. haematology vs. bone metastasis) and pain prevalence (high vs. low).

**Fig. 1 Fig1:**
[figure not shown]
Service-level Randomisation

### Methods for protecting against bias

We will recruit and randomise clusters where healthcare professionals (HCPs) have not been involved in previous phases of the research programme [22]. EPAT materials and intervention training will not be available to clusters allocated to usual care alone. We will monitor potential contamination and record details of HCP movement between clusters.

Participants, HCPs, research nurses (RNs), researchers (OR) and CTRU staff will not be blind to the cluster allocation. However, researcher (MM) will be unaware of cluster allocation when supporting telephone follow-up.

### Participant eligibility criteria

Patients with cancer will be recruited from participating oncology outpatient services to provide patient reported outcome data and medical notes review data. Patients will be eligible if they are: attending a participating outpatient service during the trial period; are aged 18 years or over; have a diagnosis of cancer; and self-report a score of ≥ 3 on the 0–10 Numerical Rating Scale (NRS) for worst pain in the past 72 h (including common pain descriptors such as: aching, unpleasant, niggling, discomfort, dull ache, cramp, throb, pinch, sharp, sting) in any part of their body. Patients will be ineligible if they are: deemed by clinical judgement to be too ill to take part (including those with severe mental health problems); considered by their clinical teams to be actively dying; unable to complete a NRS in English; not expected to be available for the first follow-up data collection (1-week). Eligibility waivers to inclusion/exclusion criteria are not permitted.

### Participant identification, approach, and recruitment

Research nurses (i.e., member of the direct care team) embedded within the clinical teams with access to clinic lists in each recruiting cluster will identify potentially eligible patients. Patients will be approached by the research nurse via a telephone call, post, or in-person. Patients approached via telephone, will be sent an invitation pack via email or post. Patients approached by post, will be invited to contact the named research nurse to express an interest in participating in the trial. Patients approached in-person (on the day of their clinic appointment) will be given a verbal description of the study, and an invitation pack to read. It is intended that most patients will be recruited via the telephone approach.

Research nurses will complete a screening log for all patients with cancer who are ≥ 18 years old and attending a participating outpatient service (first three inclusion criteria). Anonymised data on age, sex, ethnicity, year of cancer diagnosis, primary cancer type and tumour type and whether a patient is registered will be collected. Reasons patients were ineligible or declined participation will be recorded.

Informed consent will be obtained by trained research nurses prior to the patient undergoing procedures that are specifically for the purposes of the trial and are out-with standard routine care at the participating site. Patients will be able to provide informed consent over the telephone or in-person. The consent form will be sent to the CTRU via secure electronic transfer. All participants will be asked to supply their email address and telephone number, to allow telephone/SMS reminders to be sent when follow-up questionnaires are due.

Once consent and baseline questionnaires have been completed, the research nurse will register the patient to the trial using the CTRU online automated 24-h registration system. Recruitment and baseline data collection procedures are outlined in Fig. 2.

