### Description of intervention and usual care

Intervention clusters will receive EPAT plus usual care which will commence following HCP training and run for a maximum of 12-weeks per participant. The EPAT intervention will include: a training module to support clinician education; a pain screening conducted by clinic nurse/clinician (step 1); a detailed pain assessment (step 2) conducted by a physician or clinical nurse specialist for patients with a pain screen ≥ 3/10 on a 0–10 NRS of worst pain in past 72 h; a basic pain management algorithm/protocol to guide analgesic prescribing and/or onward referral to a pain specialist; and, patient resources to support self-management. EPAT will be in paper form, attached to the front of patient’s notes and implemented within existing policy. All patients with cancer (including those not recruited to the trial) attending intervention clusters that have a pain score of ≥ 3/10 will receive the intervention.

At least one HCP from each intervention cluster will take on the role of ‘EPAT champion’ to lead local implementation of the intervention, following training, with support from the trial team. Intervention champions will: have oversight of the relevant outpatient service; have direct interaction with patients and their medical notes; and have direct contact with clinical staff responsible for pain management. Oncologists and oncology nurses working in the cluster will be trained to deliver the intervention by the EPAT champion prior to the start of participant recruitment to ensure the intervention is established as routine practice. Champions will be supported by the research team via weekly catch-up calls and monthly video-call conferences with champions at other services to create a community of practice that will enable knowledge sharing. Data to support exploration of fidelity of intervention delivery will be collected. EPAT will not be available for clusters randomised to deliver usual care alone.

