## Discussion

The CAPTURE pilot trial opened to recruitment in December 2023 and recruitment is ongoing. The trial will evaluate the feasibility of conducting a phase III cluster randomised controlled trial of a standardised pain management programme (EPAT) integrated within routine care at NHS oncology outpatient services.

Previous evidence from clinical trials shows that standardising pain assessment in oncology leads to improvements in cancer patients’ pain and quality of life [10]. However, there is little literature describing the optimal ways to implement standardised pain assessment within routine care pathways in oncology outpatient services [40]. This pilot trial will address this research gap.

The strengths of the pilot trial relate to the sample size and number of clusters that will be recruited. Involving multiple sites (i.e. hospitals) and clusters (i.e. outpatient services) will help to optimise allocation of future resources by identifying and addressing logistical challenges and refining the intervention before conducting a larger-scale trial. The pilot trial will also determine the feasibility of future economic evaluation of EPAT and provide preliminary cost-effectiveness estimates. Including an embedded process evaluation enables in-depth exploration of intervention implementation, mechanisms of impact and fidelity from a participant, healthcare professional and researcher perspective. Conducting this multi-centre, cluster randomised pilot trial will provide a robust exploration of the adapted pain assessment intervention (EPAT) and an understanding of how it can be implemented in a complex healthcare system.

We acknowledge that a limitation of the trial design is that findings will be specific to the United Kingdom National Health Service. It may therefore be difficult to generalise results to other healthcare systems worldwide. There may be potential for selection bias as participants are recruited post cluster randomisation. There is also potential for contamination between clusters if healthcare professionals rotate between services and share information about the intervention. These issues will be considered carefully during the trial and will be explored within the process evaluation.

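### Unblinded research nurses choose whom to approach, and only intervention services may already hold an EPAT pain score on the notes, so identification can differ by arm and no safeguard is stated

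*Protocol article*

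**What the plan says.** All references are to the protocol article.

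- **Who identifies patients.** Under Participant identification, approach, and recruitment, the research nurses are members of the direct care team, "embedded within the clinical teams with access to clinic lists in each recruiting cluster will identify potentially eligible patients". Approach is by telephone, post or in person, mostly by telephone.
- **Blinding.** Methods for protecting against bias states: "Participants, HCPs, research nurses (RNs), researchers (OR) and CTRU staff will not be blind to the cluster allocation".
- **What exists only in intervention services.** Under Description of intervention and usual care, EPAT includes "a pain screening conducted by clinic nurse/clinician (step 1"). A detailed assessment follows for a score of 3 or more on the 0–10 scale of worst pain in the past 72 h. "EPAT will be in paper form, attached to the front of" the patient's notes. Staff are trained "prior to the start of participant recruitment to ensure the intervention is established as routine practice". The intervention reaches beyond trial participants: "All patients with cancer (including those not recruited to the trial) attending intervention clusters that have a pain score of" 3 or more. Usual-care services do not have EPAT.
- **Trial entry.** Participant eligibility criteria uses the same scale, the same cut-off and the same 72 h recall period, by self-report.
- **Screening log.** The log covers every adult cancer patient attending. The fields listed are age, sex, ethnicity, year of diagnosis, cancer and tumour type, whether registered, and reasons for ineligibility or refusal.
- **Acknowledgement.** The Discussion says: "There may be potential for selection bias as participants are recruited post cluster randomisation". Its response is that the issue will be considered during the trial and explored in the process evaluation.

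**The concern.** In any cluster trial that recruits after randomisation, a recruiter who knows the allocation can influence who enters. This design adds something more specific: in one arm only, an earlier answer to the entry question itself may be on file before the patient is approached. A nurse with a target of 15 participants has a practical reason to start with patients known to report pain. The usual-care nurse has no EPAT score to work from.

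Eligibility and recruitment rates are primary outcomes, and the Abstract lists eligibility and consent rates among the progression criteria. If patients are pre-selected on pain in one arm, the two arms' rates measure different things. Pain at baseline and follow-up could also differ between arms for reasons unrelated to EPAT, and baseline BPI enters the planned change scores.

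**Working it through.** **1. The plan's own figure.** The Sample size section starts from 60 per arm and 30% loss: 60/(1 − 0.30) = 85.7, so 86 per arm. Over 6 services per arm, 86/6 = 14.3, so 15 per service, 90 per arm and 180 in total. The stated 180 reproduces. It matters here only because it sets the quota of 15 per service.

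**2. Can a score exist before approach?** Most recruitment is by telephone, and in-person baseline measures are completed before the appointment. The current visit's EPAT screen would therefore often not yet have been done. What can exist is a score from an earlier visit, because EPAT is meant to be routine before recruitment opens and applies to all patients with pain. Table 1 shows that research nurses use medical records at screening, for contact details.

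**3. Does the common entry question remove the problem?** No. Asking every approached patient the same question standardises the decision once a patient is asked. It does not standardise who is asked.

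**4. Size of the effect on the eligibility rate.** The article gives no pain distribution, so all inputs here are assumptions.

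*Simple model.* Let p be the share with pain of 3 or more. Suppose intervention nurses approach everyone with a recorded score of 3 or more and a fraction q of the rest, with the recorded score taken as accurate. Eligibility among those approached is p/(p + (1 − p)q).

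| p | q = 1 | q = 0.5 | q = 0.25 | q = 0.1 |
|---|---|---|---|---|
| 0.30 | 0.30 | 0.46 | 0.63 | 0.81 |
| 0.50 | 0.50 | 0.67 | 0.80 | 0.91 |
| 0.70 | 0.70 | 0.82 | 0.90 | 0.96 |

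If the denominator is instead all logged patients, and usual-care nurses approach a fraction f without a score, the arms give p against p × f. For p = 0.50 and f = 0.75 that is 0.50 against 0.38. With q = f = 1 there is no distortion under either denominator.

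*Model with measurement error.* True worst pain is Normal with mean 4.5 and SD 2.0. The EPAT, entry and follow-up scores each equal true pain plus independent error (SD 1.3), rounded and limited to 0–10. EPAT has no effect, and a patient is eligible if the entry score is 3 or more. By simulation:

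- P(eligible) = 0.80
- P(eligible given EPAT score of 3 or more) = 0.89

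With mean pain 3.0 instead of 4.5, these become 0.58 and 0.79.

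**5. Size of the effect on pain.** Same model, mean 4.5, at the documents' cut-off of 3:

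| Share of intervention participants found through EPAT | Baseline difference | Follow-up difference | Difference in change |
|---|---|---|---|
| Half | 0.09 | 0.12 | about 0.04 |
| All | 0.18 | 0.25 | 0.25 − 0.18 = 0.07 |

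The Analysis section treats a reduction of 2 points or more as clinically significant, so these shifts are small. The model also holds true pain constant from the EPAT score to trial entry. In practice an earlier score of 3 or more would already have triggered EPAT management, which could lower baseline pain in that arm. The direction of any net shift is therefore unknown.

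**The case against.** The strongest objection is that nothing in the article says research nurses consult EPAT forms. The named source is the clinic list, and the stated use of records at screening is for contact details. A score from an earlier visit describes an earlier 72 h period and does not settle current eligibility. All of this stands, and it limits the point to a risk.

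Three mitigations are also real. Eligibility rests on the patient's own answer in both arms, the log covers all adult attendees in both arms, and selection bias is openly acknowledged. Registered and non-registered patients can already be compared by arm. What the listed fields cannot do is separate a patient who was never approached from one who was, and that is the step where the arms can diverge.

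It may also be said that order of approach is working detail left to the full protocol, or to the recruitment figure, which is not shown. That is fair as to the missing detail alone. The article does, however, describe identification and has a dedicated section on protection against bias. That section deals with previous staff involvement, access to EPAT materials, contamination and one blinded follow-up researcher, and says nothing on identification.

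A reader might infer more than the text supports:

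- **That identification does differ by arm and distorts the rates.** The documents show only that it can.
- **That baseline pain will be materially higher in the intervention arm.** Shifts of 0.33 points at baseline and 0.41 at follow-up appear in the same model if half the participants are found through a score of 5 or more. No such cut-off is in the documents.
- **That the pooled eligibility rate will not be the one a definitive trial sees.** A definitive cluster trial using the same recruitment procedure would have EPAT on the notes in its intervention services too.

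**Conclusion.** The point holds as an unguarded, arm-specific recruitment risk. Unblinded identification after randomisation, with a pain score on the entry scale possibly visible in one arm only, can make the eligibility and recruitment rates non-comparable between arms. This is the firmer consequence: 80% against 89% under the main assumed values, 58% against 79% with lower assumed pain, and no difference if every logged patient is asked in both arms. The effect on pain is secondary: about 0.1 points if half the intervention participants are found through a score of 3 or more, with uncertain direction.

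The percentages and point differences rest on assumed pain distributions and on nurses actually using EPAT scores, which the article does not say they do. The progression thresholds are in a table that is not shown, so whether a shift of this size would change a progression decision cannot be judged. This is a cheap improvement worth making, not a flaw that undermines the pilot.

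**What to change.** In Participant identification, approach, and recruitment, state that:

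- in both arms, patients are approached from the clinic list in the same set order, for example consecutively;
- EPAT forms and scores are not used to identify or prioritise patients for the trial;
- the screening log also records whether each patient was approached (yes/no) and by which route (telephone, post or in person).

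Report approach and eligibility rates by arm and cluster. Compare approached with not-approached patients, by arm, on the characteristics already logged.

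The cost is one working instruction and two log fields. Recruitment may be slightly slower in intervention services, because nurses could not go straight to patients with known pain. The Discussion says recruitment is ongoing, so the change would protect only the patients still to be identified. The date it takes effect should be recorded.
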